## Study participants

**Table Taba:** 

*Aim 1:*	*Participants*
Estimation of incidence and time trends of Long/Post-COVID in people with diabetes compared to those without diabetes, and analysis of potential risk factors for Long/Post COVID	All SHI-insured people in Germany (2021: 73.32 million; 2023: 74.31 million) stratified by diabetes status in the years 2021 to 2024
*Aim 2:*	
Analysis of mortality, any hospitalization, and hospitalization due to acute myocardial infarction, stroke, amputation, and DFS within 12, 24, and 36 months after Long/Post-COVID diagnosis in people with diabetes compared to those without diabetes, and identification of potential risk factors for these conditions	All SHI-insured people with and without an initial diagnosis of Long/Post-COVID, stratified according to diabetes status, will be monitored for a maximum of 36 months with regard to mortality and hospitalization due to relevant morbidity The cohort of Long/Post-COVID cases in 2021 and 2022 will be observed for up to 36 months; The cohort of Long/Post-COVID cases in 2023 will be observed for up to 12 months

### Statistical analysis

*Aim 1* The incidence rate of Long/Post-COVID will be estimated separately in the population with and without diabetes and compared as relative risks. The incidence rates will be analyzed standardized by age and sex, using the entire German population as standard population. As SHI data will be used, the person time will be calculated by summing all quarters of the insurance time of insured persons under risk. The relevant insurance time ends on the earliest of the following: the date of first diagnosis of Long/Post-COVID (index date), the end of insurance time (e.g. death) or the end of the observation period (i.e. December 31, 2023).

In addition, Poisson regression models will be used to examine the time trend of the incidence rate of Long/Post-COVID. Since only 3 years will be available, we will only compare the incidence rates of 2022 and 2023 with those of the year 2021 as reference category. Moreover, the impact of potential risk factors such as age, sex, comorbidities (CHD, COPD, asthma, obesity, depression) and region (urban vs. rural, Eastern vs. Western Germany) will be analyzed with these models. We will consider each comorbidity as well as region separately in order to explore their role independently. We will estimate incidence rates stratified by diabetes and these variables. We further plan to perform regression models adjusted for each variable and diabetes as well as models stratified by diabetes. Thus, we intend to explore whether obesity is a further confounder or effect modifier in our analysis, even in the light of probable underreporting in administrative data. To take into account over-dispersion of the outcome variable, all analyses were conducted with the de-scale adjustment [22].

*Aim 2* Age- and sex-standardized mortality and hospitalization rates will be estimated within 12, 24, and 36 months after a Long/Post-COVID diagnosis between 2021 and 2024. The data base will be a population-based cohort consisting of all insured persons with an inpatient or outpatient Long/Post-COVID diagnosis. All mortality and hospitalization rates will be calculated separately for insured people with and those without diabetes and will be compared using relative risks. In order to overcome potential confounding, Cox regression models will further be performed to investigate the impact of the aforementioned potential risk factors, as well as the year of Long/Post-COVID diagnosis. As we will conduct Cox models, we will only assess the time to first hospitalization with the date of hospital admission as index date. We will also consider death as competing risk in analyses with hospitalization as outcome.

Sensitivity analyses:Estimation of incidence rate of Long/Post-COVID in the population with and without diabetes and the corresponding relative risks as decribed in aim 1 using only insured persons with an outpatient or inpatient COVID-19 diagnosis as population at riskRepetition of analyses of aim 2 using only persons with an inpatient or outpatient Long/Post-COVID diagnosis and an additional previous COVID-19 diagnosis as population at riskExpansion of the outcome “Long/Post-COVID” to include comparable differential diagnoses (functional and somatoform disorders) in order to minimize the risk of bias resulting from potential underreporting of Long/Post-COVIDComparison of people with Long/Post-COVID and those with a differential diagnosis, stratified according to diabetes statusRepetition of main analyses of aim 1 and aim 2 with the modified outcome.

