## Abstract

**Background:**

Several studies have shown that people with diabetes are at higher risk of experiencing a severe course of COVID-19 infection. However, it remains unclear whether diabetes per se is a risk factor for the development of Long/Post-COVID. In addition, there is a lack of nationwide, population-based studies on the epidemiology of Long/Post-COVID in people with diabetes. The aim of this project is to analyze: (1) incidence and time trends of Long/Post-COVID in people with and without diabetes between 2021 and 2023 in Germany as well as potential risk factors; (2) mortality, any hospitalization and hospitalization due to acute myocardial infarction, stroke, amputation and diabetic foot syndrome (DFS) after a Long/Post-COVID diagnosis, including an analysis of potential risk factors.

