### Role of diabetes

Diabetes mellitus is a widespread chronic disease with a global prevalence of 11.1% among adults aged 20 to 79 [12]. Diabetes mellitus is regarded as a risk factor for severe COVID-19, as indicated by increased rates of hospitalization, intensive care admission, and mortality [13]. However, it is not yet clear whether having diabetes per se is also a risk factor for developing Long/Post-COVID. A systematic review on this topic found that 44% of the studies identified diabetes as a risk factor for Long/Post-COVID, although the strength of this association varied considerably between studies [14]. This was partly due to the quality or design of the studies, e.g., a different definition of Long/Post-COVID, study population and study size, and the length of the observation period. In addition, no studies in Germany have yet compared the incidence of Long/Post-COVID in people with diabetes to people without diabetes.

People with diabetes exhibit chronic hyperglycemia, immune dysregulation, endothelial dysfunction, and a pro-inflammatory and prothrombotic state, which may exacerbate acute infection and promote persistent post-viral pathologies. In line with these mechanisms, studies suggest that diabetes mellitus may contribute to adverse long-term outcomes following SARS-CoV-2 infection including cardiovascular conditions [15, 16]. However, the association between diabetes and Long/Post-COVID, as well as its potential cardiovascular sequelae, remains incompletely understood.

Aims of this study are: 1) to estimate the incidence and time trends of Long/Post-COVID in people with diabetes compared to those without diabetes and to analyze potential risk factors for Long/Post-COVID; 2) to analyze mortality, any hospitalization, and hospitalization due to acute myocardial infarction, stroke, amputation, and DFS within 12, 24, and 36 months after Long/Post-COVID diagnosis in people with diabetes compared to those without, and to identify potential risk factors for these conditions.

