The inclusion of U08.9 was based on the WHO Definition [20] and on the German national S1 guideline “Long/Post-Covid” [3]. Data from published studies also confirm widespread use of U08.9 diagnosis: For instance, the study of Ollila et al., [21] showed the distribution of codes used in Post-Covid-Syndrom: U09.9! = 12.1% and U08.9 = 47.4%. The rationale for including U08.9 was a higher sensitivity in identifying patients with probable Long/Post-COVID manifestations. The ICD code G93.3 will be taken into account only for patients with a previous COVID-19 infection. For ICD codes U09.9!,U08.9 and U10.9, a single code entry is sufficient.

In addition, the analyses will be repeated for insured persons with an outpatient or inpatient COVID-19 diagnosis (ICD: U07.1) between 2020 and 2024 as a risk population (see the following section, “Sensitivity analyses”).

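### The main Aim 1 relative risk in all insured people mixes infection risk with risk after infection, so on its own it cannot answer whether diabetes per se is a risk factor; the analysis in people with a COVID-19 diagnosis measures a different quantity

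*Protocol article*

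**What the plan says.** The abstract of the protocol article says that "it remains unclear whether diabetes per se is a risk factor for the development of Long/Post-COVID", and the section Role of diabetes repeats the point. The first aim is then worded as an estimation task, "to estimate the incidence and time trends of Long/Post-COVID in people with diabetes compared to those without diabetes", together with an analysis of potential risk factors.

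The Study participants table gives the Aim 1 population as "All SHI-insured people in Germany (2021: 73.32 million; 2023: 74.31 million) stratified by diabetes status". Under Statistical analysis the contrast is defined: "The incidence rate of Long/Post-COVID will be estimated separately in the population with and without diabetes and compared as relative risks". For the denominator, "the person time will be calculated by summing all quarters of the insurance time of insured persons under risk". Follow-up ends at first Long/Post-COVID diagnosis, end of insurance or the end of 2023. Rates are standardized by age and sex. The Poisson models add comorbidities and region, but the article lists no variable for infection.

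Study design and data sources adds that "the analyses will be repeated for insured persons with an outpatient or inpatient COVID-19 diagnosis (ICD: U07.1) between 2020 and 2024", as a risk population. The Statistical analysis section lists this restriction among the sensitivity analyses. The abstract describes the purpose of the sensitivity analyses as dealing with uncertainty in diagnosing Long/Post-COVID, for example underreporting.

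The limitations in the Discussion cover misclassified Long/Post-COVID coding, missing symptom severity, residual confounding such as vaccination status, and the lack of stratification by diabetes type. They do not mention that people with and without diabetes may differ in how often they are infected, tested or given a U07.1 code.

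**The concern.** By the definitions in the article's Background section, Long/Post-COVID follows a SARS-CoV-2 infection. People who were never infected cannot develop it, yet they contribute person-time to the main analysis. If people with diabetes are infected more or less often than others, the main relative risk moves away from 1 even when diabetes has no effect on what happens after infection. A real effect after infection can likewise be hidden. Standardizing for age and sex, or adjusting for the listed comorbidities and region, does not remove a remaining difference in infection.

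Restricting to people with a COVID-19 diagnosis changes the denominator from insured people to diagnosed people, and with it the quantity estimated. It does not test how robust the all-insured ratio is to uncertain Long/Post-COVID coding, which is the stated reason for the sensitivity analyses. A reader who takes the two as versions of one estimate could read agreement as confirmation, or disagreement as instability, when neither follows.

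At stake is the sentence that the final report may write about diabetes as a risk factor.

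**Working it through.** **No figure to reproduce.** The article states no target effect, expected event count, or infection ratio by diabetes status.

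**Inputs**
- From the article: 73.32 million insured in 2021 (Study participants table); 11.1% global diabetes prevalence in adults aged 20 to 79 (Role of diabetes); almost 50% of the population registered as SARS-CoV-2-positive (Background).
- Assumed: diabetes prevalence 8% to 11.1% of the insured; coded Long/Post-COVID incidence 0.1% to 1% per year; true infection ratio (diabetes versus no diabetes) 0.80 to 1.25; a five-fold variance as an over-dispersion case. If about half of people without diabetes were infected, the infection ratio could not exceed 1/0.5 = 2.0.

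**Step 1: what the all-insured ratio contains.** Because the condition requires infection,

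RR(all insured) ≈ RR(true infection) × RR(Long/Post-COVID given infection).

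| RR given infection | infection ratio 0.80 | 0.90 | 1.00 | 1.10 | 1.25 |
|---|---|---|---|---|---|
| 1.00 | 0.80 | 0.90 | 1.00 | 1.10 | 1.25 |
| 1.10 | 0.88 | 0.99 | 1.10 | 1.21 | 1.375 |
| 1.20 | 0.96 | 1.08 | 1.20 | 1.32 | 1.50 |

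The all-insured ratio equals the ratio after infection only when the infection ratio is 1. With no effect after infection, the all-insured ratio simply reproduces the infection ratio. With 1.10 after infection, an infection ratio of 0.90 gives 0.99 and one of 0.80 gives 0.88.

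**Step 2: would sampling error mask this?** The 95% limits are the estimate divided and multiplied by exp(1.96 × √(1/d + 1/n)), where d and n are the cases with and without diabetes in one year.
- Prevalence 8%, incidence 0.1%: d = 73.32 million × 0.08 × 0.001 ≈ 5,866; n = 73.32 million × 0.92 × 0.001 ≈ 67,454; factor 1.027.
- Prevalence 11.1%, incidence 1%: d = 73.32 million × 0.111 × 0.01 ≈ 81,385; n = 73.32 million × 0.889 × 0.01 ≈ 651,815; factor 1.007.
- With five times the variance, the factors become 1.061 and 1.016.

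Under these assumptions, a shift of 10% from infection alone would look like a precise finding. This does not show that such a shift exists.

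**Step 3: does the formula hold for recorded U07.1?** Not exactly. Study design and data sources requires a previous COVID-19 infection only for G93.3. For U09.9!, U08.9 and U10.9, one entry is enough, so cases without a U07.1 code count in the all-insured analysis. Suppose true infection is equal (ratio 1.00), U07.1 recording has a ratio of 0.90, and Long/Post-COVID coding does not depend on whether U07.1 was recorded, with no effect of diabetes after infection. The all-insured ratio is then 1.00 and the ratio among the recorded is 1.00, but multiplying the recorded ratio by the latter gives 0.90 × 1.00 = 0.90. The table in step 1 therefore applies to true infection, and a U07.1 ratio can inform interpretation but not give an exact decomposition.

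**The case against.** The strongest reply is that Aim 1 is estimation. The words per se stand in the rationale and not in the aim, no hypothesis test is stated, and the abstract cites a lack of nationwide, population-based studies. For that purpose all insured people are a natural denominator, and a ratio that includes differences in infection is a legitimate overall association. This stands, and it is why the all-insured ratio should be kept. It does not settle the matter, because Aim 1 also covers risk factors and the article puts the per se question directly before its aims without saying which ratio speaks to it.

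A reader might infer that nothing ranks the two analyses, so the authors could choose after seeing both. The article does not support that: one is the main analysis, the other is labelled a sensitivity analysis, and both are in print. A detailed rule for discordant results may also sit in a full protocol or analysis plan that is not shown, so its absence is no finding.

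A reader might also infer that the restricted ratio is the clean answer. It is not. It conditions on a recorded diagnosis. The article itself describes diabetes as a risk factor for severe COVID-19, which may change who receives a U07.1 code.

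Finally, it is tempting to allow a per se claim only when both ratios point the same way. That could block a correct claim: with 1.10 after infection and an infection ratio of 0.80, the all-insured ratio is 0.88.

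**Conclusion.** The point holds as one of labelling and interpretation. The main Aim 1 relative risk is a valid measure of population burden or overall association, but it cannot by itself show whether diabetes raises the risk of Long/Post-COVID after infection. The analysis among people with a COVID-19 diagnosis addresses that more closely, imperfectly, and is a separate quantity rather than a sensitivity analysis of the first. The Discussion does not name differing infection, testing or recording as a limitation.

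The size cannot be derived from the article. Every infection ratio used here is an assumption, and nothing in the text indicates a direction. The narrow confidence limits, themselves based on assumed prevalence and incidence, show only that a distortion of several per cent could look precise if present. It would go too far to say that the main result is biased by a known amount or that the main analysis is invalid. This is a worthwhile, inexpensive improvement.

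**What to change.** In Statistical analysis, including its list of sensitivity analyses:
- Name two separate quantities. The all-insured ratio describes population burden or overall association. The ratio among people with a COVID-19 diagnosis addresses risk after infection, and should no longer be presented as a sensitivity analysis of the first.
- State that no conclusion about diabetes per se will be drawn from the all-insured ratio alone.
- Report both ratios side by side, with the age- and sex-standardized relative incidence of a first U07.1 diagnosis by diabetes status. Present the latter as context, not as an exact factor linking the two.

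In the Discussion, add differing infection, testing and U07.1 recording by diabetes status as a limitation of both ratios.

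The cost is a few sentences and one table from the same data, since both relative risks are already planned. The downside is that U07.1 is likely to be incompletely recorded, perhaps differently by diabetes status, so the conditional ratio has its own selection and must be reported with that caveat.

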## Methods/design

### Study design and data sources

This study is planned as a non-interventional longitudinal observational study based on secondary data from the SHI in Germany. The data holder is the Health Data Lab which hosts SHI data and facilitates their analysis through secure remote processing.

The SHI data contains comprehensive information on inpatient and outpatient care with exact dates, diagnoses, prescriptions, and some sociodemographic factors (age, gender, place of residence (urban/rural)). The diabetes status of insured persons is defined according to an established algorithm based on antihyperglycemic prescriptions and outpatient and inpatient diagnoses [17]. A diagnosis of Long/Post-COVID is considered as first or incident event per se (no counting of reinfections), as this diagnosis has only been established since 2021. In light of the clinically heterogeneous presentation of Long/Post-COVID and the documented supposed inconsistencies in ICD-10 coding practices across healthcare settings, we define Long/Post-COVID on the basis of the following diagnostic coding: U08.9 (Personal history of COVID-19, unspecified; this code is used if a previous confirmed COVID-19 infection affects a person's health or leads to the use of healthcare services), U09.9! (Post-COVID-19 condition, unspecified;), U10.9 (Multisystem inflammatory syndrome associated with COVID-19, unspecified), or G93.3 (Myalgische Enzephalomyelitis/Chronisches Fatigue-Syndrom (ME/CFS). The Studies at Charité – University Medicine Berlin, which represent a major reference for research on Long/Post-COVID and ME/CFS, have shown that post-COVID syndrome can persist for more than 20 months after infection and encompass the full spectrum of post-infectious ME/CFS [18, 19]. The main features are moderate to severe fatigue and exercise intolerance, which meet the Canadian consensus criteria for ME/CFS.

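### The Aim 1 time trend takes the code's launch year, 2021, as its only reference, so the 2022 and 2023 rate ratios mix code introduction with disease incidence

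*Protocol article*

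**What the plan says.** Under Study design and data sources, a Long/Post-COVID diagnosis is "considered as first or incident event per se (no counting of reinfections), as this diagnosis has only been established since 2021". One entry of U08.9, U09.9! or U10.9 is enough to make a case. U08.9 is described as a history code, with no stated limit on the time since infection. The same section reports that "post-COVID syndrome can persist for more than 20 months after infection", and it recognises infections before 2021: a repeat analysis takes as its risk population "insured persons with an outpatient or inpatient COVID-19 diagnosis (ICD: U07.1) between 2020 and 2024".

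Under Statistical analysis, Aim 1, person-time is summed over insurance quarters up to the end of 2023. The Poisson trend model is fixed as follows: "Since only 3 years will be available, we will only compare the incidence rates of 2022 and 2023 with those of the year 2021", with 2021 as reference category.

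The article states no run-in, washout or alternative baseline for the trend. The limitations in the Discussion mention variation in coding across healthcare settings, but not the introduction of the codes.

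**The concern.** The launch of a code guarantees that a code recorded in 2021 is the person's first. It does not show that the illness began in 2021. Someone ill since mid-2020 could not be coded until the code existed, and would then be counted as a new case of 2021. By 2022 the code had been available for a year, so this backlog should fall mainly on the reference year, which both planned contrasts share.

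Time trends are a named objective of Aim 1. In a population of more than 73 million, confidence intervals will be very narrow, so a launch artefact would be reported with apparent certainty as a change in disease incidence.

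**Working it through.** The article gives no expected rate, event count or rate ratio for the trend, so there is no figure to reproduce. The check is an expression for the bias, filled with assumed values.

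**Inputs from the article:** reference year 2021; every first code incident; diagnosis available since 2021; insured population 73.32 million (2021) and 74.31 million (2023).

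**Assumed, because the article gives no values:** b21 and b22, the shares of first codes in 2021 and 2022 that are backlog; u, the share of true 2021 cases left uncoded in the launch year; the incidence; the overdispersion factor.

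**Step 1, general form.** If N true new cases arise in 2021, the coded count is N(1−u)/(1−b21). Taking 2022 coding as complete, observed ratio / true ratio = [(1−b21)/(1−b22)] / (1−u).

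**Step 2, backlog confined to 2021 (b22 = 0, u = 0).** The factor is 1−b21:
- b21 = 5%: 0.95
- b21 = 10%: 0.90
- b21 = 20%: 0.80
- b21 = 30%: 0.70
- b21 = 40%: 0.60

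A true ratio of 1.25 would read 1.25 × 0.80 = 1.00 at 20% and 1.25 × 0.70 = 0.875 at 30%, which reverses the trend.

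**Step 3, backlog spilling into 2022.** With b21 = 20% and b22 = 5%, the factor is 0.80/0.95 = 0.84 rather than 0.80.

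**Step 4, launch-year under-coding.** With b21 = 20% and b22 = 0:
- u = 0%: 0.80
- u = 10%: 0.80/0.90 = 0.89
- u = 20%: 0.80/0.80 = 1.00
- u = 30%: 0.80/0.70 = 1.14

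The sign changes within a plausible-looking range, so the net direction is open.

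**Step 5, precision.** The half-width of the 95% interval on the log ratio is 1.96 × √(1/E1 + 1/E2). At an assumed 1 per 1,000 person-years, E1 = 73,320 and E2 = 74,310, giving 0.010. At 10 per 1,000, E1 = 733,200 and E2 = 743,100, giving 0.003. An assumed overdispersion factor of 10 multiplies these by √10, to 0.032 and 0.010. Sampling error would not hide a bias of the size in Step 2.

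**Step 6, diabetes strata.** An equal backlog share in both strata cancels from the diabetes relative risk. If it were 10% in one stratum and 20% in the other, the two trends would differ by a spurious factor of 0.90/0.80 = 1.125.

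**Step 7, does a stated sensitivity analysis remove the effect?** The repetition among people with a recorded COVID-19 diagnosis includes 2020 infections. For Aim 1 it names incidence rates and relative risks by diabetes status, and it states no different rule for a first code. It does not.

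**The case against.** The strongest reply is that no direction of bias has been shown. New codes tend to be under-used at first, which pushes the ratios upward, and Step 4 shows this can cancel or outweigh the backlog. That stands. A reader might infer that 2021 is inflated and that the trend is biased downward by a known factor of 1−b; the article supports neither.

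Four further points have force:
- The persistence statement says the syndrome can last that long. It gives no share of patients who do, so the size of the backlog is unknown.
- Not every 2021 first code after a 2020 infection is backlog. The Background sets onset at 4 or 12 weeks after infection, so infections late in 2020 properly yield new cases in 2021. Removing them all would deflate 2021 and bias the ratios upward.
- Making 2022 the reference category is not a cure by itself. With year as a three-level factor, 2023 versus 2022 is already the quotient of the two planned ratios, and the model fit is unchanged.
- Use of 2024 data in Aim 2 and in the COVID-19 risk population does not show that 2024 is meant for the Aim 1 trend. Only the Aim 1 row of the Study participants table extends to 2024.

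A reader might also infer that the diabetes relative risk is biased. That needs a backlog share that differs by diabetes status, and the article gives no reason to expect one.

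Finally, the rates can be read simply as rates of first diagnosis. But the stated aim is incidence and time trends of Long/Post-COVID, and under the plan as written a change in first coding would be reported as that trend.

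**Conclusion.** The concern holds in limited form. The article infers incidence from the novelty of the code and then uses the launch year as the only baseline. Both planned rate ratios therefore combine disease incidence with two launch effects of opposite sign: prevalent backlog and low initial uptake. No stated sensitivity analysis or limitation deals with this.

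The size and net sign cannot be established. The range of 0.95 to 0.60 rests on an assumed backlog of 5% to 40%, all of it in 2021, with no under-coding; spillover into 2022 or under-coding moves it toward or past 1. What is established is that the planned contrasts cannot separate these effects and that precision will be far too high for sampling error to mask them. This merits a change before analysis, because it touches a named objective and the remedy is cheap.

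**What to change.** 1. Model the Aim 1 trend by calendar quarter, which the quarterly person-time already supports. Treat the first quarters of 2021 as a code run-in and exclude them from the reference, at least in a pre-specified sensitivity analysis. Report the 2023 versus 2022 ratio explicitly as the contrast least affected by launch, though not free of spillover.
2. As a sensitivity analysis, split 2021 first codes by date of the U07.1 diagnosis. Set aside only those whose infection was early enough for the 4- or 12-week definition to have been met within 2020. Counting back 28 or 84 days from 31 December 2020 gives cut-offs of about 3 December and 8 October 2020. Do not remove all 2020 infections. People without a recorded U07.1 cannot be classified, and their number should be shown.
3. Describe the outcome as a first coded diagnosis, and state the launch-year artefact as a limitation of the trend.
4. Reconcile the Aim 1 period: 2021 to 2023 in the Abstract and in Statistical analysis, but 2021 to 2024 in the Study participants table. If 2024 data are available for Aim 1, include that year in the trend.

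Items 1 to 3 cost some protocol wording and a modest amount of code on data the plan already uses. Item 4 costs wording only, unless 2024 is added, which lengthens the Aim 1 observation period. The downside is a slightly longer analysis in which the comparison with 2021 is no longer the sole headline trend.

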### Comorbidities / risk factors

Several studies described the association between certain comorbidities and the development of Long/Post-COVID (e.g. systematic review by Tsampasian et al. 2023 [11]):

Conditions associated with an increased risk of Long/Post-COVID include:Coronary heart disease (CHD): A meta-analysis of five studies with 201,906 patients reported a significantly increased risk of Long/Post-COVID among patients with pre-existing CHD (OR 1.28; 95% CI 1.19–1.38).Chronic obstructive pulmonary disease (COPD): A meta-analysis of 10 studies including a total of 257,340 patients found that COPD was a risk factor associated with the development of Long/Post-COVID (OR 1.38; 95% CI 1.08–1.78).Bronchial asthma: A meta-analysis of 13 studies involving 639,397 patients showed that patients with asthma had a significantly higher risk of developing Long/Post-COVID (OR 1.24; 95% CI 1.15–1.35).Anxiety and/or depression: A pooled analysis of four studies including a total of 634,734 patients found that the risk of Long/Post-COVID was significantly increased in patients suffering from anxiety or depression (OR 1.19; 95% CI 1.02–1.40).

Other diseases (e.g. chronic kidney disease, malignancies, and autoimmune disorders) encompass broad and clinically heterogeneous conditions that are difficult to capture with sufficient specificity using ICD codes in routine data.

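### Aim 1 examines comorbidities and region one at a time to find their independent roles, so no described model adjusts the diabetes relative risk for the comorbidities together

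*Protocol article*

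**What the plan says.** The Aim 1 text of the Statistical analysis section has three layers.

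- **Main comparison.** Incidence rates with and without diabetes are compared as relative risks: "The incidence rates will be analyzed standardized by age and sex, using the entire German population as standard population".
- **Risk factors.** Poisson models are to examine "potential risk factors such as age, sex, comorbidities (CHD, COPD, asthma, obesity, depression) and region (urban vs. rural, Eastern vs. Western Germany"). The approach for comorbidities and region is then fixed, with a reason: "We will consider each comorbidity as well as region separately in order to explore their role independently".
- **Models.** "We further plan to perform regression models adjusted for each variable and diabetes as well as models stratified by diabetes". Obesity is singled out: "we intend to explore whether obesity is a further confounder or effect modifier in our analysis".

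No Aim 1 model holding diabetes and all the comorbidities together is described. For Aim 2, the same section turns to Cox regression on the same factors with the declared purpose of dealing with confounding. Aim 1 has no counterpart to that statement.

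The abstract says "it remains unclear whether diabetes per se is a risk factor for the development of Long/Post-COVID", and Role of diabetes repeats that "it is not yet clear whether having diabetes per se is also a risk factor for developing Long/Post-COVID".

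**The concern.** The reason given for the separate models is one that separate models cannot serve. CHD, COPD, asthma, obesity and depression can be expected to occur together and to be more common in people with diabetes. A ratio from a model that leaves the other factors out carries part of their effect. Mutual adjustment is the usual way to approach an independent role.

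The diabetes ratio is affected most directly. The section Comorbidities / risk factors cites CHD ("OR 1.28; 95% CI 1.19–1.38"), COPD, asthma and anxiety or depression as raising the risk of the outcome. Any of these that is more common in diabetes, after age and sex are accounted for, moves the diabetes ratio away from what diabetes does by itself. The plan would produce several diabetes ratios, each adjusted for a different single factor. None is adjusted for all of them, and none is named as the answer to the open question.

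Sampling error will not hide this. The Study participants table gives 73.32 million insured people in 2021 and 74.31 million in 2023, so a bias of a few percent could matter more to the interpretation than chance does.

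**Working it through.** The article states no figure on this point that could be reproduced. What follows is an illustration of size.

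**Inputs from the article** (Comorbidities / risk factors), with odds ratios used as rate ratios: CHD 1.28, COPD 1.38, asthma 1.24, anxiety or depression 1.19 (used for depression).

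**Assumed inputs**, because the article gives none:
- a true diabetes ratio of 1.00;
- prevalences with/without diabetes, understood as after age and sex standardization:
  - low: CHD 12/8%, COPD 8/6%, asthma 8/7%, depression 15/12%;
  - mid: 20/8%, 12/6%, 10/7%, 20/12%;
  - high: 30/8%, 18/6%, 14/7%, 28/12%;
- obesity, where included: 45/18%, ratio 1.1 to 1.5.

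**Step 1: bias in the diabetes ratio from one omitted factor.** With p1 and p0 the prevalences with and without diabetes:

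bias = (1 + p1(RR − 1)) / (1 + p0(RR − 1))

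Mid case:
- CHD: (1 + 0.20 × 0.28)/(1 + 0.08 × 0.28) = 1.0560/1.0224 = 1.0329
- COPD: 1.0456/1.0228 = 1.0223
- Asthma: 1.0240/1.0168 = 1.0071
- Depression: 1.0380/1.0228 = 1.0149

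If the factors are independent given diabetes, the biases multiply: 1.0329 × 1.0223 × 1.0071 × 1.0149 ≈ 1.079. This is the ratio with no comorbidity adjustment.

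**Step 2: adjust for one factor**, dividing the product by that factor's bias.

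| Adjusted for | Low | Mid | High |
|---|---|---|---|
| none | 1.027 | 1.079 | 1.159 |
| CHD | 1.015 | 1.045 | 1.093 |
| COPD | 1.019 | 1.056 | 1.110 |
| Asthma | 1.024 | 1.072 | 1.140 |
| Depression | 1.021 | 1.063 | 1.126 |
| all jointly | 1.00 | 1.00 | 1.00 |

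**Step 3: add obesity.** At a ratio of 1.5 its bias is (1 + 0.45 × 0.5)/(1 + 0.18 × 0.5) = 1.225/1.090 = 1.124. The mid-case ratio without adjustment becomes 1.213. Adjusting for CHD alone leaves 1.213/1.0329 = 1.17, and for asthma alone 1.213/1.0071 = 1.20. Adjusting for obesity alone returns 1.079. Over all scenarios, with an obesity ratio of 1.1 to 1.5, the CHD-only model gives 1.04 to 1.23. In the most extreme corner (high prevalences, obesity ratio 1.5), the asthma-only model gives 1.303/1.0165 = 1.28.

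**Step 4: the comorbidity ratios themselves.** Poisson models were fitted to expected counts for the mid case, with an assumed diabetes prevalence of 10%. Clustering was induced by multiplying the odds of every comorbidity by a factor in one half of the population and dividing by it in the other half.

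| Model | CHD | COPD | Asthma | Depression |
|---|---|---|---|---|
| diabetes + one factor, no clustering | 1.28 | 1.38 | 1.24 | 1.19 |
| diabetes + one factor, moderate (1.5) | 1.29 | 1.39 | 1.25 | 1.20 |
| diabetes + one factor, strong (2.5) | 1.34 | 1.44 | 1.30 | 1.25 |
| joint model, all cases | 1.28 | 1.38 | 1.24 | 1.19 |

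The diabetes ratio is therefore biased even without clustering. The comorbidity ratios are biased only to the extent that comorbidities cluster given diabetes.

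**The case against.** **The wording leaves room.** Adjusting for each variable and diabetes could mean one model with all variables, and considering comorbidities separately could mean separate terms instead of a composite score. A condensed article may also leave covariate lists to the full plan. That reading is possible but hard to square with the sentence on separate consideration, which states a method and its reason. If a joint model is intended, the two sentences still need to be reconciled.

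**Stronger readings a reader might infer.**
- *That the diabetes ratio is never adjusted for more than one factor.* The article does not support this. The main comparison is standardized by age and sex together, and the sentence on separate consideration covers only comorbidities and region.
- *That the diabetes per se question is the worded aim.* It is the stated knowledge gap. The aims are incidence and time trends by diabetes status and potential risk factors, which an age- and sex-standardized comparison serves. No test or decision rule is attached to the diabetes ratio.
- *That every comorbidity ratio will be badly confounded.* That depends on clustering the article does not describe. Under moderate assumed clustering the shift is about 0.01.
- *That a bias near 1.2 is to be expected.* It needs a strong obesity effect, for which the article cites no ratio, and good recording, whereas the article expects obesity to be underreported.

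**A joint model is not automatically the better answer.** CHD may lie on the pathway from diabetes to the outcome. The jointly adjusted ratio would then leave out part of the diabetes effect. This stands, and it is why the joint result should sit beside the standardized ratio. Looking at factors one by one is also a reasonable exploratory step, provided it is labelled so.

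**Conclusion.** The point holds as a flaw in a stated method. Separate models cannot show independent roles of correlated factors, and no described Aim 1 model gives a diabetes ratio adjusted jointly for the comorbidities that the article itself cites as risk factors. The Discussion's remark on residual confounding gives vaccination status, which is unavailable, as its example and does not mention the measured comorbidities.

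The size is illustrative and may be modest: a few percent in the mid case without obesity, and larger only if obesity is strong and well recorded. The direction (a diabetes ratio that is too high) holds as long as these conditions raise the risk, are more common in diabetes after standardization, and act as confounders and not as mediators. The change should be made, but the standardized comparison itself is not invalid.

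**What to change.** - Add one pre-specified Poisson model for Aim 1 with diabetes, age, sex, calendar year, region, obesity, CHD, COPD, asthma and depression together.
- Report it as a nested sequence: age, sex and year; plus obesity; plus the remaining factors. Show it beside the age- and sex-standardized ratio, not in place of it.
- State that the fully adjusted ratio may exclude effects mediated through CHD, and say which ratio in the sequence addresses the diabetes per se question.
- Keep the single-factor and diabetes-stratified models, labelled exploratory, and delete *independently* from the sentence that introduces them.

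The cost is one more set of models on variables already planned, and more careful wording where a comorbidity may be a mediator.
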